### Treatment

2.6

#### Group assignment and masking

2.6.1

Randomisation is performed centrally at the Julius Center for Health Sciences and Primary Care, University Medical Center Utrecht. A web-based application with a minimisation procedure is used. Stratification is performed for gender, age and general functioning. The following people are blinded: participants receiving the treatment, persons administering the treatment, persons assessing the outcomes, persons analysing the data. Trial treatment randomisation codes are not available to the study staff, but are available at the local pharmacy for emergency unblinding.

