### Aims and objectives

2.1

The primary aim of this study is to investigate whether raloxifene augmentation compared to placebo is effective in reducing positive, negative and general symptoms and in improving cognitive functioning. Symptoms are measured by the positive and negative syndrome scale (PANSS) [40] and cognitive function is measured with the Brief Assessment of Cognition in Schizophrenia (BACS) [41]. The BACS consists of 6 tasks measuring different domains of cognitive functioning: list learning (verbal memory), verbal fluency (categorical instances and letter fluency, verbal fluency/processing speed), digit sequencing (working memory), symbol coding (processing speed), Token Motor Task (motor speed/processing speed), and the Tower of London Test (reasoning and problem solving).

Secondary outcome variables include general functioning, measured with the personal and social performance (PSP) [42]; severity of thought disorder, measured with the Thought And Language Disorder scale (TALD) [43]; health-related quality of life and quality adjusted life years (QALYs), measured with the EQ-5D-5L [31]; use of healthcare and non-healthcare resources, measured with the institute for Medical Technology Assessment's Medical Consumption Questionnaire (iMTA-MCQ) and Productivity Cost Questionnaire (iMTA-PCQ) respectively and depressive symptoms, measured with Beck's Depression Inventory (BDI) [32]. The Brief Negative Symptom Scale (BNSS) [44] is used to measure negative symptoms with a higher sensitivity [44].

Genetic, hormonal, and inflammatory biomarkers are assessed to predict treatment response. DNA-samples are collected in saliva. Serum hormonal biomarkers include for women prolactin, follicle-stimulating hormone (FSH) and 17β-estradiol, and for men prolactin, 17β-estradiol, free-testosterone and sex hormone-binding globulin (SHBG). Inflammation is measured as C-reactive protein (CRP) in serum.

Safety data are evaluated by comparing incidences of key Serious Adverse Events (SAEs) and Suspected Unexpected Serious Adverse Reactions (SUSARs) between groups, e.g. hospitalisations.

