#### Primary study parameters

2.8.2

The primary analysis will include change in psychotic symptoms as measured by the PANSS at 6 and 12 weeks of treatment (end-of-treatment) and at 6 months after end of treatment and change in cognitive functioning as measured by the BACS at 12 weeks of treatment (end-of-treatment) and at 6 months after end of treatment. A mixed model for repeated measurements will be used, including at least time point, treatment group, the interaction between time point and treatment, sex and age as fixed factors, baseline PANSS/BACS-score, concomitant antipsychotic medication which will be converted to mean daily olanzapine equivalent dose [47], current drug and alcohol use as covariate and subject as random intercept factor. More specifically, the primary analysis will be a repeated measures analysis of variance (ANOVA) with time as within factor (baseline, 6 weeks and 12 weeks of treatment) and treatment as between factor (raloxifene or placebo), with symptom severity (PANSS total, positive, negative or general scores) as dependent variables. For the analysis of cognitive function, the BACS-scores of each of the six domains will be converted into six separate and a composite Z-score for each participant, controlling for age and gender [48]. Separate repeated measures ANOVAs will be performed for the separate *Z*-scores as dependent variables, time as within factor (baseline and 12 weeks of treatment) and treatment as between factor (raloxifene or placebo). The contrast between raloxifene and placebo at 6 and 12 weeks of treatment will be presented with a 95% confidence interval for the difference between the treatment arms. In addition, post-hoc analyses will be conducted to investigate differences at individual time points. There will be corrected for multiple testing by adjusting the p-values produced by each statistical test for each outcome using the Holm method [49,50].

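### General functioning is a minimisation factor but is not among the listed primary model terms; if it is prognostic, the test is mildly conservative and some precision is forgone.

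*Protocol article*

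**What the plan says.** Group assignment and masking (2.6.1) describes central allocation: "A web-based application with a minimisation procedure is used". It then names three factors: "Stratification is performed for gender, age and general functioning". It does not name the instrument for general functioning, its categories or the allocation probability.

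Primary study parameters (2.8.2) gives a mixed model "including at least time point, treatment group, the interaction between time point and treatment, sex and age as fixed factors". The list continues with "baseline PANSS/BACS-score, concomitant antipsychotic medication which will be converted to mean daily olanzapine equivalent dose" and ends with "current drug and alcohol use as covariate and subject as random intercept factor". General functioning is not in it, and no reason is given.

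The same section then restates the analysis: "More specifically, the primary analysis will be a repeated measures analysis of variance (ANOVA) with time as within factor". Treatment is the between factor, and no other term is named. For the BACS, the Z-scores themselves control for age and gender. For the PANSS, this description carries none of the three minimisation factors.

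Aims and objectives (2.1) ties general functioning to an instrument, but only as an outcome: "Secondary outcome variables include general functioning, measured with the personal and social performance (PSP"). Table 1 shows that the PSP is collected at baseline.

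**The concern.** Minimising on a prognostic factor makes the arms more alike on it than chance would, so the treatment difference varies less from trial to trial. A model that omits the factor does not register this. The variation it explains stays in the residual, and the reported standard error is larger than the true one. Intervals are then too wide and the test rejects too seldom under the null. The trial also forgoes the precision that adjustment would give.

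There is some reason to expect general functioning to be prognostic. The Introduction and the Discussion both link functioning closely to negative symptoms and cognition, and the trial team chose to balance on it. The listed model adjusts for several variables that did not govern allocation and leaves out one that did.

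**Working it through.** **Inputs.** From Power and sample size calculation (2.8.1): standardised effect 0.57, two-sided alpha 5%, power 80%, 50 evaluable per arm, 10% dropout, 110 in total. Assumed: R2, the share of outcome variance that general functioning explains given the other covariates. The article gives no value, so a range from 0 to 0.20 is used.

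**The plan's own figure.** n per arm = 2(1.96 + 0.84)² / 0.57² = 2 × 7.84 / 0.3249 = 48.3, so 49 by the normal approximation. The two-sample t-test gives 49.3, so 50. With 50 × 1.1 = 55 per arm, the total is 110. The stated size reproduces. Power at 50 per arm is 81.3% (normal) or 80.6% (t-test).

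**Effect of omitting the factor.** Take one end-of-treatment contrast with residual SD 1 before adjustment for functioning. SE = √(2/50) = 0.20 and d/SE = 0.57/0.20 = 2.85. Let k = √(1 − R2). If the factor is almost perfectly balanced:

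- reported SE / true SE = 1/k
- true type I error = 2Φ(−1.96/k)
- power, factor omitted = Φ((2.85 − 1.96)/k)
- power, factor included = Φ(2.85/k − 1.96)

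For R2 = 0.10, k = 0.949. The SE ratio is 1.054 and type I error is 2Φ(−2.07) = 3.9%. Power is Φ(0.94) = 82.6% omitted and Φ(1.04) = 85.2% included.

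| Assumed R2 | SE ratio | Type I error, omitted | Power, omitted | Power, included | Forgone (points) |
|---|---|---|---|---|---|
| 0 | 1.000 | 5.0% | 81.3% | 81.3% | 0 |
| 0.02 | 1.010 | 4.8% | 81.6% | 82.1% | 0.5 |
| 0.05 | 1.026 | 4.4% | 81.9% | 83.3% | 1.3 |
| 0.10 | 1.054 | 3.9% | 82.6% | 85.2% | 2.6 |
| 0.20 | 1.118 | 2.8% | 84.0% | 89.0% | 5.0 |

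**Check by simulation.** Minimisation on three two-level factors, with an assumed biased-coin probability of 0.8, n = 100 and 4,000 runs per scenario. The fitted model held the other two factors and a baseline covariate, with or without functioning.

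| Assumed R2 | Null rejection, omitted | Null rejection, included | Power, omitted | Power, included |
|---|---|---|---|---|
| 0 | 5.1% | 5.0% | 80.4% | 80.3% |
| 0.02 | 4.9% | 5.2% | 81.1% | 81.5% |
| 0.05 | 4.5% | 5.1% | 81.3% | 82.4% |
| 0.10 | 4.5% | 5.2% | 81.6% | 84.7% |
| 0.20 | 3.4% | 5.4% | 82.1% | 87.9% |

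The direction agrees. With a random element in the allocation, balance is imperfect, so the test is less conservative than the formula says: 3.4% against 2.8% at R2 = 0.20. The SE and type I columns of the first table are therefore upper bounds on the conservatism. Forgone power stays close to the formula: 82.4 − 81.3 = 1.1 points at R2 = 0.05, and 87.9 − 82.1 = 5.8 at 0.20, the latter slightly above the formula's 5.0.

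**The case against.** **The covariate list is a minimum.** Its opening words allow further terms, the analysis plan is not shown, and an article condenses a fuller protocol. This stands to the extent that nothing excludes general functioning, so a reader should not infer a fixed decision to leave it out. But the text permits the term without committing to it. It names covariates that played no part in allocation, and its narrower ANOVA description adds none.

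**The baseline score may already do the work.** A reader might infer that the model adjusts for nothing beyond sex and age. It does not stop there: it lists baseline PANSS/BACS score, antipsychotic dose and substance use. What counts is how far functioning predicts outcome beyond these, and the article says nothing on that. The link it draws between functioning and symptoms is not evidence of a partial correlation given baseline. This stands, and is why the range starts at zero.

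**The formula assumes near-perfect balance.** Minimisation usually balances categories and includes a random element. If functioning were split at the median (an assumption, with normal scores), about 64% of a linear effect would be balanced. At a partial correlation of 0.4, type I error would then be about 3.9% rather than the formula's 3.3%. This stands as well.

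**The planned power is not at risk.** A reader might infer that the trial is underpowered as a result. The sample size used an unadjusted effect size, and power with the factor omitted is 81.3% to 84.0% by formula and 80.4% to 82.1% in simulation. Nor does the omission bias the estimate or inflate false positives. The loss exists only against the better model.

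**Conclusion.** The mismatch is real and its direction is clear, but it is small. One of three minimisation factors is missing from the listed primary model, and for the PANSS all three are missing from the ANOVA description. If general functioning is prognostic beyond the listed covariates, the analysis is mildly conservative. Over an assumed partial R2 of 0 to 0.20, type I error lies between 5% and about 3%, the lower end being the most conservative case. Forgone power is 0 to about 5 points, and about 1 point at R2 of 0.05 or less. If functioning adds nothing beyond the baseline score, nothing is lost.

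These figures rest on the assumed R2, a single end-of-treatment contrast and 50 evaluable per arm. That the PSP is the measure used for minimisation is an inference: the allocation section names no instrument. The point is a free improvement to the analysis, not a threat to the trial's validity or its planned power.

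**What to change.** Add baseline general functioning as a covariate alongside sex and age in the primary and secondary efficacy models, in the form used for minimisation. State which instrument and categories that is; it is presumably the PSP. Where the PSP is itself the outcome, its baseline value can serve as this term. If the sponsor prefers to leave the factor out, the plan should say why.

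Give the mixed model and the repeated measures ANOVA under Primary study parameters the same set of terms, so that both carry all three minimisation factors. Settle this before unblinding, so that the covariate is not chosen after results are seen.

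The cost is about one degree of freedom among roughly 100 evaluable participants (one fewer than the number of categories if a multi-level grouping is used). No new data are needed: the factor is already recorded for allocation, and the PSP is already collected at baseline.

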#### Medication

2.6.2

Participants are randomised to either raloxifene (Raloxifene Teva, EU/I/10/627/001–003), or placebo treatment. The study medication is prescribed by one of the medical doctors involved in this study and taken orally at a daily fixed dosage of 120 mg raloxifene or placebo. Raloxifene Teva 60 mg tablets contain 60 mg raloxifene hydrochloride (HCl), corresponding with 54 mg raloxifene. Placebo tablets filled with the commonly used excipients lactose monohydrate, microcrystalline cellulose and magnesium stearate. Manufacturing of placebo tablets and packaging of the raloxifene and placebo tablets in equal packaging was performed by ACE Pharmaceuticals BV. Raloxifene and placebo tablets have the same external appearance. The study medication is dispensed in two boxes of 92 tablets, handed out at the baseline visit and at visit 2(6 weeks post-baseline).

#### Treatment duration

2.6.3

Thus far, the duration of trials using raloxifene, in patients with schizophrenia ranged from 6 to 24 weeks [36]. The majority of these trials included specifically postmenopausal women and showed that a treatment duration of 12 weeks is effective in improving symptoms. However, in men and premenopausal women with schizophrenia, raloxifene has only been tested during a period of 8 and 6 weeks, respectively [29,37]. As an intermediate step in the process towards developing long-term treatments for all groups of patients (i.e. pre- and postmenopausal women and men), we decided to give raloxifene during 12 weeks, to be able to investigate prolonged efficacy and monitor the potential risks and side effects in especially men and premenopausal women. When our study proves that 120 mg/day is safe also for men and premenopausal women with schizophrenia, this opens the door to longer trials. These trials could be open-label when efficacy is replicated in the current (double blind) trial.

### Safety

2.7

Medical history and current medication use are checked at baseline and treatment visits. Blood is screened at baseline for triglycerides, cholesterols, kidney and liver function. If a moderate elevation of triglycerides or liver enzymes is found (<3 times the ULN), these parameters will be measured at each treatment visit.

Physical examination is performed at baseline (visit 1) and end of treatment (visit 3), and blood pressure is measured at baseline and every treatment visit, as hypertension is a known side effect of raloxifene. Pregnancy tests are performed in all WOCBP, at baseline and every treatment visit. In case a patient reports any side effects at any time-point, thorough physical examination will be conducted at the earliest convenience. Furthermore, if appropriate, blood will be drawn. Study continuation or termination is based on the exclusion criteria 7 to 11 as defined in section 2.4.2.

#### Adverse events

2.7.1

Adverse events (AEs) are defined as any undesirable experience befalling a subject during the course of the study, whether or not it is related to the investigational product. All AEs that are reported by the subject or are observed by the study team are recorded. Side effects and health issues are checked during all treatment visits. The patient will be asked an open-ended question for experience of any side effect or health problems that occurred since the previous visit. The patient fills out the adjusted Green Climacteric Scale [46] and the investigator explicitly questions the occurrence of any thromboembolic event, as these include the most common and most serious side effects of raloxifene. Serious Adverse Events (SAEs) are recorded and reported.

#### Data and safety monitoring board (DSMB)

2.7.2

A Data Safety Monitoring Board (DSMB) has been implemented in this study. The DSMB consists of experts in the field of the study (i.e. a statistician, a psychiatrist and a gynaecologist) who are completely independent from the study. Members should not have any competing interests that could impact the trial. The DSMB aims to safeguard the interests of trial participants, assess the safety and efficacy of the interventions during the trial, and monitor the overall conduct of the trial. In addition, it aims to assist and advise the sponsor and Principal Investigators in order to protect the validity and credibility of the study, without violating the concepts behind the original protocol. The DSMB receives and reviews the progress and accruing data of the trial on an annual basis. Based on this information, the DSM makes recommendations to the sponsor of the study. Potential recommendations are: no action needed (1), premature termination of the trial (2) or proposing protocol changes (3). Should the sponsor decide not to fully implement the advice of the DSMB, the sponsor will send the advice to the reviewing medical ethical review board; including a note to substantiate why (part of) the advice of the DSMB will not be followed.

### Statistical analyses

2.8

Unless otherwise specified, a two-sided 0.05 level of significance will be used to declare treatment arms significantly different. Intention-To-Treat analyses will be conducted. All statistical analyses will be performed using SPSS for Windows (version 25.0.0.2) or other widely accepted statistical or graphical software.

#### Power and sample size calculation

2.8.1

For the sample size calculation, a medium effect size of 0.57 was assumed, which is similar to the effect size for symptom severity detected in the most recent meta-analysis and the effect size for cognition [36,37]. Sample size calculation was based on disjunctive power (or minimal power), which is the probability of finding at least one true intervention effect across all of the outcomes. To be able to find an effect size of 0.57, with two sided alpha set at 5% and with 80% power, 50 participants in each group have to be evaluated. Since we expect some 10% dropout, a total of 55 participants per arm are needed, resulting in a total of 110 participants.

#### Primary study parameters

2.8.2

The primary analysis will include change in psychotic symptoms as measured by the PANSS at 6 and 12 weeks of treatment (end-of-treatment) and at 6 months after end of treatment and change in cognitive functioning as measured by the BACS at 12 weeks of treatment (end-of-treatment) and at 6 months after end of treatment. A mixed model for repeated measurements will be used, including at least time point, treatment group, the interaction between time point and treatment, sex and age as fixed factors, baseline PANSS/BACS-score, concomitant antipsychotic medication which will be converted to mean daily olanzapine equivalent dose [47], current drug and alcohol use as covariate and subject as random intercept factor. More specifically, the primary analysis will be a repeated measures analysis of variance (ANOVA) with time as within factor (baseline, 6 weeks and 12 weeks of treatment) and treatment as between factor (raloxifene or placebo), with symptom severity (PANSS total, positive, negative or general scores) as dependent variables. For the analysis of cognitive function, the BACS-scores of each of the six domains will be converted into six separate and a composite Z-score for each participant, controlling for age and gender [48]. Separate repeated measures ANOVAs will be performed for the separate *Z*-scores as dependent variables, time as within factor (baseline and 12 weeks of treatment) and treatment as between factor (raloxifene or placebo). The contrast between raloxifene and placebo at 6 and 12 weeks of treatment will be presented with a 95% confidence interval for the difference between the treatment arms. In addition, post-hoc analyses will be conducted to investigate differences at individual time points. There will be corrected for multiple testing by adjusting the p-values produced by each statistical test for each outcome using the Holm method [49,50].

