## Abstract

Although acute psychotic symptoms are often reduced by antipsychotic treatment, many patients with schizophrenia are impaired in daily functioning due to the persistence of negative and cognitive symptoms. Raloxifene, a Selective Estrogen Receptor Modulator (SERM) has been shown to be an effective adjunctive treatment in schizophrenia. Yet, there is a paucity in evidence for raloxifene efficacy in men and premenopausal women. We report the design of a study that aims to replicate earlier findings concerning the efficacy of raloxifene augmentation in reducing persisting symptoms and cognitive impairment in postmenopausal women, and to extend these findings to a male and peri/premenopausal population of patients with schizophrenia. The study is a multisite, placebo-controlled, double-blind, randomised clinical trial in approximately 110 adult men and women with schizophrenia. Participants are randomised 1:1 to adjunctive raloxifene 120 mg or placebo daily during 12 weeks. The treatment phase includes measurements at three time points (week 0, 6 and 12), followed by a follow-up period of two years. The primary outcome measure is change in symptom severity, as measured with the Positive and Negative Syndrome Scale (PANSS), and cognition, as measured with the Brief Assessment of Cognition in Schizophrenia (BACS). Secondary outcome measures include social functioning and quality of life. Genetic, hormonal and inflammatory biomarkers are measured to assess potential associations with treatment effects. If it becomes apparent that raloxifene reduces psychotic symptoms and/or improves cognition, social functioning and/or quality of life as compared to placebo, implementation of raloxifene in clinical psychiatric practice can be considered.

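### The random subject intercept imposes equal variance and equal correlation at all visits, so the visit-specific PANSS intervals and p-values may be miscalibrated if either changes over time

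*Protocol article*

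**What the plan says.** Section 2.8.2 (Primary study parameters) of the protocol article describes the model in these terms: "A mixed model for repeated measurements will be used, including at least time point, treatment group, the interaction between time point and treatment". Baseline score is a covariate, and the list ends with "current drug and alcohol use as covariate and subject as random intercept factor". The section names no residual covariance structure, robust standard error or sphericity correction.

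PANSS enters the primary analysis at weeks 6 and 12 and at 6 months after treatment ends (week 38 in Table 1). BACS enters at week 12 and at 6 months only.

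The inference is visit by visit: "The contrast between raloxifene and placebo at 6 and 12 weeks of treatment will be presented with a 95% confidence interval". Post-hoc tests at individual time points and Holm-adjusted p-values follow.

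The sentence after the mixed model restates the primary analysis as a repeated-measures ANOVA. Its time levels are baseline, week 6 and week 12 for PANSS, and baseline and week 12 for BACS.

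**The concern.** A random intercept with independent, equal-variance residuals is compound symmetry. Each visit's treatment contrast then gets a standard error from a variance pooled over all modelled visits. If the baseline-adjusted variance at a visit is above that pooled value, its interval is too narrow and its test rejects too often. If it is below, the interval is too wide and power is lost.

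The PANSS visits are unevenly spaced: 6 weeks between the first two, then 26 weeks to the third, which falls after treatment has stopped. Baseline may also predict week 6 better than week 12. Equal variance and equal correlation are therefore a real restriction on the error bars of the primary contrasts, and nothing in the article supports it.

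**Working it through.** **The plan's own figure first.** The inputs from sections 2.8 and 2.8.1 are "a two-sided 0.05 level of significance will be used to declare treatment arms significantly different", "a medium effect size of 0.57 was assumed" and "with two sided alpha set at 5% and with 80% power, 50 participants in each group have to be evaluated".

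- Normal approximation: 2 × (1.960 + 0.842)² / 0.57² = 48.3, so 49 per arm. The t-test solution is 49.3, so 50 per arm, with power 0.806 at 50.
- Dropout: 50 × 1.10 = 55 per arm and 110 in total, as stated. Dividing instead, 50 / 0.90 = 55.6, gives 56 and 112, a difference of two patients.

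The figure reproduces. It is a two-group comparison that uses no within-patient covariance, so this point does not change it.

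**Analytic check.** With complete, balanced data, the true variance of the contrast at visit *j* is (2/n) × σ²ⱼ. The random-intercept model reports (2/n) × the mean of the visit variances. So:

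- variance ratio at visit *j* = σ²ⱼ / mean(σ²)
- actual type I error = 2 × [1 − Φ(1.96 / √ratio)]

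The SDs below are assumed baseline-adjusted SDs, because the article gives none.

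| Visits modelled | Assumed SDs | Mean variance | Week 6 | Week 12 | Month 6 |
|---|---|---|---|---|---|
| 6, 12 | 10, 10 | 100 | 5.0% | 5.0% | – |
| 6, 12 | 10, 12 | 122 | 3.0% | 7.1% | – |
| 6, 12 | 9, 12 | 112.5 | 2.1% | 8.3% | – |
| 6, 12, 38 | 10, 12, 12 | 129.3 | 2.6% | 6.3% | 6.3% |
| 6, 12, 38 | 10, 12, 14 | 146.7 | 1.8% | 4.8% | 9.0% |

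For the second row at week 12: 144 / 122 = 1.18, 1.96 / √1.18 = 1.80, giving 7.1%. The nominal 95% interval then covers about 93%.

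**Simulation.** The random-intercept model was fitted by REML under the null, with 50 per arm, baseline as covariate and 10% missing after week 6. There were 4,000 runs per case, with a Monte Carlo standard error of about 0.35 points. AR means that correlation decays with each visit step, baseline included.

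| Assumed truth | Visits modelled | Week 6 | Week 12 | Month 6 |
|---|---|---|---|---|
| Compound symmetry, r = 0.7 | 6, 12 | 4.7% | 4.8% | – |
| Compound symmetry, r = 0.7 | 6, 12, 38 | 4.9% | 4.9% | 4.6% |
| AR 0.7 | 6, 12 | 3.7% | 7.0% | – |
| AR 0.8 | 6, 12 | 2.8% | 8.0% | – |
| r = 0.7, SD 20% larger at week 12 | 6, 12 | 3.6% | 7.5% | – |
| AR 0.7 | 6, 12, 38 | 2.6% | 5.4% | 8.2% |
| AR 0.8 | 6, 12, 38 | 1.7% | 4.8% | 8.5% |
| AR 0.8, SDs 1, 1.1, 1.2 | 6, 12, 38 | 0.4% | 5.0% | 10.9% |

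Every simulated departure from compound symmetry leaves at least one visit off nominal. Which visit, and in which direction, depends on the visits modelled.

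**The ANOVA description.** Here baseline is an outcome level, so correlations matter as well. Assume equal SDs (set to 1), correlation 0.75 for weeks 0–6 and 6–12, and 0.60 for weeks 0–12. The variances of the differences, 2(1 − r), are 0.5, 0.5 and 0.8, with mean 0.6. A pooled-error test of the change from baseline to week 12 has variance ratio 0.8 / 0.6 = 1.33 and type I error of about 9.0%. An ANOVA that compared the arms separately at each visit would use that visit's own variance and avoid the problem. The text does not say which is meant.

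**The case against.** The best defence is that the article does not exclude a residual structure. Its model list is a minimum, a mixed model can carry a residual covariance alongside a random intercept, and the full protocol or analysis plan is not shown. Degrees-of-freedom method and convergence fallback are ordinary analysis-plan detail, and their absence here is no fault. What does not fall away is that the article states one within-patient structure and commits to no other. Followed as written, it gives compound symmetry.

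Four stronger readings are tempting, and the article does not support them.

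- **That the intervals are miscalibrated.** No visit SD or correlation is given, and under true compound symmetry the error is nominal.
- **That the week-12 interval is necessarily too narrow.** The 7% to 8% figures come from modelling weeks 6 and 12 only. Section 2.8.2 also places the 6-month visit in the primary analysis, and week 12 is then close to nominal in most cases tested.
- **That equal correlation does the damage throughout.** With two post-baseline outcomes there is only one correlation, so only the equal-variance restriction acts. Equal correlation matters once the 6-month visit, or baseline as an outcome, is included.
- **That BACS is equally affected.** It has no week-6 assessment, and an ANOVA with two time levels meets sphericity trivially. The week-6 versus week-12 point is for PANSS only, although a BACS mixed model would still pool week 12 with month 6.

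It is also fair to object that changing the covariance wording alone would leave the ANOVA sentence standing. That stands, and the fix has to cover both.

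**Conclusion.** The point holds as a conditional risk to the visit-specific PANSS inference. The named random intercept imposes compound symmetry, and the nominal 5% and 95% levels depend on that being true.

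On assumed covariances, a 20% rise in SD with only weeks 6 and 12 modelled puts week 12 at about 7% and week 6 at about 3%. With the 6-month visit in the model, the likelier costs are a conservative week-6 test and, in the simulated cases, a liberal month-6 test; week 12 moves little. These ranges rest wholly on the assumed SDs and correlations and are not estimates for this trial. The planned 50 evaluable and 55 enrolled per arm stand. This is a cheap improvement to the analysis wording.

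**What to change.** In section 2.8.2:

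1. Make the baseline-adjusted mixed model the single primary analysis, and reconcile or remove the sentence that restates it as a repeated-measures ANOVA.
2. Replace the random subject intercept with an unstructured within-subject covariance over the post-baseline visits, fitted by REML, with Satterthwaite or Kenward-Roger degrees of freedom where the software offers them.
3. Pre-specify heterogeneous compound symmetry as the fallback if the unstructured model does not converge.

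Each visit then has its own variance, so the assumption is no longer needed. The cost is a few lines of wording and 3 covariance parameters for two visits (2 × 3 / 2) or 6 for three (3 × 4 / 2), estimated from about 100 patients. The SPSS MIXED procedure offers the structure in its REPEATED statement. The downside is a small risk of non-convergence, which the fallback covers.
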